### Statistical methods for primary and secondary outcomes {20a}

Statistical description.Detailed description of cases of withdrawal and censoring, including the time and reason for censoring.Descriptive statistics: Based on their distribution, data will be presented as either the mean and standard deviation, or the median with maximum, minimum, and confidence interval, or the number and frequency (%), among others.Statistical inference method.Measurement data: The paired t-test, analysis of variance, the rank-sum test, signed rank-sum test, and the median test will be used.Counting data: The chi-square test, Fisher exact test, and others will be used; grade data will be analyzed using the ridit test and the Cochran–Mantel–Haenszel test.Primary outcome analysis: Per protocol set analysis and full analysis set analysis will be performed. The Cochran-Mantel-Haenszel test will be used for multicenter counts and analysis of covariance for measures. For the confounding factors that are difficult to control or are uncontrolled before allocation, the least-squares means of the analysis of covariance and their 95% confidence limit or logistic regression will be used as covariates to determine the between-group efficacy.Two-sided difference tests will be used to assess statistical differences, and a difference with a p-value of ≤ 0.05 will be considered to be statistically significant.

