##### Treatment 1: Shengji ointment

Size: 30 g/box.Formulation: Ointment.Usage and dosage: For external use. The ointment will be spread on skimmed cotton and applied to the affected area.Route of administration: Topical.Frequency of administration: Once every 24 h.Treatment course: Four weeks.Manufacturer: Tianjin Darentang Jingwanhong Pharmaceutical Co., Ltd, Tianjin, Tianjin, China.

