#### Secondary outcomes

As secondary outcomes, we will determine the wound healing rate, amputation rate and extent, granulation time, and Maryland Foot Score.

Wound healing rate = (Original wound area - unhealed wound area)/Original wound area ×100%.Amputation extent: A extensive amputation refers to an amputation above the ankle, while a limited amputation refers to an amputation below the ankle. The amputation level will be identified in a multidisciplinary team of vascular surgeons and orthopedic foot and diabetes specialists according to the results of the lower limb angiography.Granulation time (days): The period of time within which new granulation tissue appears within the wound.The Maryland Foot Score will be determined to evaluate foot function, including the presence or absence of pain. The maximum score is 100 points, > 89 points indicate excellent function, 75–89 points good function, 50–74 average, and < 50 points poor function.

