#### Other indicators of treatment efficacy

We will also record the following parameters:

Clearance time (days): The period from enrollment (day 0) to the complete clearance of degenerated and necrotic tendon tissue.

Granulation tissue score: Evaluation of scores at enrollment (day 0), visit 2 (week 2), and at the end of the trial (week 4).

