#### Participant timeline {13}

The time schedule of the enrollment, interventions, assessments, and visits for the participants in this trial is shown in Table 1.

**Table 1 Tab1:** Study time-period

	STUDY PERIOD			
	Enrolment	Allocation	Post-allocation	Close-out
TIMEPOINT	-1 day	0 day	After 14 days	After 28 days
ENROLLMENT:				
Eligibility screen	●			
Informed consent	●			
Allocation		●		
INTERVENTIONS:				
Treatment group: Shengji ointment and Pineapple protease (bromelain)		●	●	●
Control group: Comfeel® Plus wound dressing		●	●	●
ASSESSMENTS:				
Demographic data	●			
Medical history and allergy history	●			
Vital signs		●	●	●
Physical examination		●	●	●
Blood routine + C- reactive protein		●		●
Urine routine		●		●
Routine stool + occult blood		●		●
Liver function		●		●
Renal function		●		●
Electrocardiogram		●		●
Urine pregnancy test		●		
Wound coverage rate		●	●	●
Wound healing rate		●	●	●
Amputation extent			●	●
Granulation time			●	●
Maryland Foot Score		●	●	●
Clearance time			●	●
Granulation tissue score		●		●
Adverse events		●	●	●

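### Granulation time and clearance time are censorable times to an event, but the listed tests need a complete value for every patient and no rule says how a patient without the event is scored

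*Protocol article*

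**What the plan says.** The protocol article defines two outcomes in days. Under Secondary outcomes: "Granulation time (days): The period of time within which new granulation tissue appears within the wound". No start point is given. Under Other indicators of treatment efficacy: "Clearance time (days): The period from enrollment (day 0) to the complete clearance of degenerated and necrotic tendon tissue". Neither definition gives a value for a patient in whom the event does not occur. Table 1 (Participant timeline {13}) marks both at the day 14 and day 28 visits only, and day 28 closes the study.

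The statistical methods section {20a} expects censoring. It promises "Detailed description of cases of withdrawal and censoring, including the time and reason for censoring". For inference on measurement data it then lists: "The paired t-test, analysis of variance, the rank-sum test, signed rank-sum test, and the median test will be used". It assigns no listed test to either time outcome. The Data management section {19} carries the last observation forward in the full analysis set.

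On a related item, the text fixes the granulation tissue score as "Evaluation of scores at enrollment (day 0), visit 2 (week 2), and at the end of the trial (week 4"), while Table 1 marks that score at day 0 and day 28 only.

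**The concern.** Some patients will be event-free when observation stops. The protocol lets the researcher withdraw patients who reach a clinical endpoint such as the need for surgery, names perceived ineffectiveness as a reason for leaving, and allows for 20% loss. The listed tests need one number per patient. Carrying an observation forward does not create that number, because an event-free patient has no event time to carry.

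An analyst following the text must therefore improvise. Event-free patients can be dropped, kept at day 28 or at a worst rank, or given their last day seen as though it were the event day. Dropping them compares speed only among patients who reached the event, so a treatment that brings more patients to the event gets little credit. Using the last day seen scores an early withdrawal as a fast success. In an open-label trial, a choice with such different results should be fixed in advance.

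**Working it through.** **Inputs.** From the protocol: two-sided alpha 0.05, 1:1 allocation, 72 evaluable per arm, 20% loss, follow-up to day 28. The dropout step reproduces: 72 / (1 − 0.20) = 90. The protocol gives no event rate, power or effect size for either time outcome, so there is no figure of its own to reproduce here. The 50% and 71% in the sample-size section are rates of an undefined effectiveness. They are borrowed as an assumption, and a range is shown.

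**What conditioning on the event does.** With constant hazards, λ = −ln(1 − p)/28.
- Control: −ln(0.50)/28 = 0.02476 per day. Treatment: −ln(0.29)/28 = 0.04421 per day. Hazard ratio 0.04421/0.02476 = 1.79.
- Mean time among those with the event by day 28 is 1/λ − 28(1 − p)/p.
- Control: 40.40 − 28 × 0.50/0.50 = 12.4 days. Treatment: 22.62 − 28 × 0.29/0.71 = 11.2 days.

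A hazard ratio of 1.79 shrinks to a difference of 1.2 days.

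**Power by handling rule.** Simulation with 72 per arm, proportional hazards, censoring at day 28 and 1,500 runs per scenario. The Monte Carlo standard error near 77% is √(0.77 × 0.23/1500), about 1.1 points. Ranges cover Weibull shapes 1 and 2. Figures are power in %.

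| Event by day 28 (control v treatment) | Log-rank, daily dates | Log-rank, day 14/28 only | Rank-sum, all kept (day 28 or worst rank) | Rank-sum, event patients only, daily dates | Rank-sum, event patients only, day 14/28 |
|---|---|---|---|---|---|
| 30% v 46% | 50.5–52.5 | 49.5–51.6 | 47.9–51.8 | 5.5–6.5 | 4.7–5.7 |
| 50% v 71% | 76.6 | 74.8–76.3 | 72.3–74.3 | 10.1–10.5 | 8.3–10.1 |
| 70% v 87.7% | 82.8–83.3 | 79.4–81.5 | 76.1–78.2 | 20.9–23.3 | 15.9–18.8 |
| 80% v 93.5% | 82.8–85.1 | 77.6–79.1 | 76.6–76.9 | 34.4–35.6 | 24.5–27.9 |
| 90% v 97.7% | 80.9–81.6 | 70.9–72.3 | 69.5–70.3 | 46.3–47.1 | 36.1–37.7 |
| 99% v 99.93% | 75.8–77.3 | 49.2–61.3 | 65.5–66.5 | 62.9–63.1 | 38.5–55.3 |

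Dropping event-free patients is what destroys power, and the loss shrinks as events become common. The two-visit grid costs little at low to moderate event rates and matters only when nearly everyone has the event.

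**Last day seen entered as the event day.** Simulation with 90 per arm and constant hazards; the withdrawal rates are assumptions.
- 50% event rate in both arms, withdrawal 30% control and 10% treatment: the rank-sum test rejects in about 26% of trials although there is no effect, because the arm with more withdrawals looks faster.
- 50% v 71%, same withdrawal: power falls to about 30%.
- Equal 20% withdrawal: type I error is held, and power at 50% v 71% is about 69%.

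**Granulation tissue score.** The text names three time points (day 0, week 2, week 4). Table 1 marks two (day 0, day 28). They cannot both be followed.

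**The case against.** A reader might infer that event-free patients are excluded and that the comparison therefore loses almost all its power. The document does not say so. No section removes them, membership of the full analysis set does not depend on either event, and carrying observations forward points to keeping patients in. A rank-sum test can place event-free patients at a worst rank, and a median test needs only above or below the median. With everyone kept, power is close to that of the log-rank test. The 10% figure belongs to one possible rule at borrowed event rates. First appearance of granulation could be much more common than 50%.

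A reader might also infer from Table 1 that a time can only be 14, 28 or never. That overreads it. The same table marks treatment only at visits although the text says "Frequency of administration: Once every 24 h", so the marks show visits and an onset date could be noted at one. Daily assessment is not stated either.

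Finally, this is a condensed article, and endpoint-level detail may sit in an analysis plan that is not shown.

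The first two objections limit the size of the point and are accepted. The third holds only in part. The article does fix a list of methods and a carry-forward rule, it acknowledges censoring, and what it fixes does not suit these two outcomes. The mismatch over the granulation tissue score is unaffected by any of this.

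**Conclusion.** The concern holds in a limited form. Two time-to-event outcomes are paired with tests that have no means of handling censoring and with an imputation rule that cannot give a valid event time. The size depends on what the analyst then does. At 50% v 71% and 72 per arm, power is about 72–74% if all patients are kept at day 28 or worst rank, about 10% if event-free patients are dropped, and about 77% for log-rank. At 90% v 97.7%, dropping gives 46–47% against 81–82% for log-rank. If the last day seen is used, unequal withdrawal can create a difference where none exists.

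These figures rest on proportional hazards, the assumed event rates and, for the last rule, assumed withdrawal rates. The visit schedule is not the main cause. Both outcomes are non-primary, so the main conclusion of the trial is unaffected, but the change is worth making.

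**What to change.** State in the analysis plan, before the data are analysed:
- Compare granulation time and clearance time with Kaplan-Meier curves and a log-rank test. Use event dates where they were recorded. If only day 14 and day 28 status exists, use a grouped or interval-censored version, which keeps about 75–76% power in the 50% v 71% scenario.
- Censor event-free patients at day 28 or at their last assessment, and do not apply last observation carried forward to these two times.
- Treat amputation or withdrawal for surgery as a competing event, with cumulative incidence curves in place of Kaplan-Meier where such events occur.
- Start both clocks at day 0, so that granulation time has a stated origin like clearance time.
- Reconcile Table 1 with the text on the week-2 granulation tissue score, and report whether that score was collected.

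The cost is some wording and slightly more analysis work. Recruitment was expected to end in December 2022 and the article appeared in October 2023, so new daily date fields may come too late. The analysis changes do not depend on them.

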### Outcomes {12}

#### Primary outcome

The wound coverage with granulation tissue will be the primary outcome. The development of granulation tissue will be assessed as follows:

$$\text{Wound coverage rate} = \text{The wound area covered by granulation tissue}\, (\text{mm}^{2})/\text{Whole wound area}\, (\text{mm}^{2}) \times 100\%$$

We will use three-dimensional scanning to obtain the wound surface topography and the inSight® platform (eKare, Inc., Fairfax, VA, USA) to identify the different tissue types and to measure the areas covered by them.

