#### Sample size {14}

The sample size was calculated using Pass 11.0 software (NCSS Statistical software https://www.ncss.com/software/pass). Based on a preliminary review of the literature and the clinical practice and experience of the Second Affiliated Hospital of Tianjin University of Traditional Chinese Medicine in the treatment of diabetic foot ulcers, the control group is expected to have an effectiveness of 50%, and the treatment group of 71%. Postulating a patient ratio of 1:1 between groups and an alpha of 0.05 on both sides, 72 patients would be required in each group. Assuming a 20% loss to follow-up, we calculated a number of 90 patients in each group and a total of 180 patients as the target sample size.

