#### Sequence generation {16a}

Using a central random system and minimization algorithm, the allocation probability of the target group will be calculated for each enrolled patient for them to be assigned to the most suitable treatment group and ensuring a balance of control factors between the groups. The controlling factors are (1) ulcer location (plantar, dorsum of foot, or toe), and (2) ABI evaluation index (> 0.7, and ≤ 0.7).

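### The only stated covariate rule points away from the two minimisation factors; ulcer location and ABI stratum should be named in the primary analysis

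*Protocol article*

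**What the plan says.** Sequence generation {16a} assigns patients "Using a central random system and minimization algorithm". It names the factors to be balanced: "The controlling factors are (1) ulcer location (plantar, dorsum of foot, or toe), and (2) ABI evaluation index (> 0.7, and ≤ 0.7").

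Statistical methods {20a} first gives the general form of the primary analysis: "The Cochran-Mantel-Haenszel test will be used for multicenter counts and analysis of covariance for measures". It names no covariates and no strata beyond the reference to centres. Adjustment comes in the next sentence. It opens with "For the confounding factors that are difficult to control or are uncontrolled before allocation" and continues that "the least-squares means of the analysis of covariance and their 95% confidence limit or logistic regression will be used as covariates". The wording is garbled, since a method cannot be a covariate, but the sense is that ANCOVA or logistic regression will adjust for factors of that class.

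The outcome at issue is in Primary outcome: "The wound coverage with granulation tissue will be the primary outcome", expressed as a percentage of the wound area. Sample size {14} instead works with response rates: "the control group is expected to have an effectiveness of 50%, and the treatment group of 71" per cent. For that reason both a continuous and a binary analysis are examined below.

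**The concern.** Minimisation removes most of the chance difference between arms in the factors it balances. An analysis that ignores those factors still counts the outcome variation they cause as noise. Its reported standard error then exceeds the true sampling error of the treatment difference, its type I error drops below 5%, and it has less power than the design could give. The usual principle is therefore that factors used to balance allocation also enter the analysis.

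The article's rule runs the other way. The allocation section calls location and ABI controlled factors, and the analysis section directs adjustment to factors that were not controlled. An analysis plan that followed this sentence literally would leave out the two variables it most needs. This is more than a missing covariate list: it is a stated selection rule that points in the wrong direction.

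**Working it through.** **1. The text.** Location and ABI are controlled at allocation. The adjustment rule is for factors that are hard to control or uncontrolled before allocation. Taken literally, the two sets do not overlap, and neither factor is named anywhere in the analysis text.

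**2. Inputs.** From Sample size {14}: 72 evaluable patients per arm, two-sided 5%, 1:1, 50% versus 71%. From Sequence generation {16a}: one three-level and one two-level factor. Assumed, because the documents do not give it: how prognostic the factors are.

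**3. The plan's own figure.** The loss-to-follow-up step reproduces: 72/(1 − 0.20) = 90 per arm, 180 in total. The 72 itself does not reproduce at 80% power, which needs 84 per arm. With 72, the null standard error is √(2 × 0.605 × 0.395/72) = 0.0815 and the alternative standard error is √((0.25 + 0.2059)/72) = 0.0796. Power is Φ((0.21 − 1.96 × 0.0815)/0.0796) = 73.6%. No power is stated. That is a separate matter; only n = 72 is carried forward.

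**4. Continuous outcome.** Suppose the two factors explain a share R² of the outcome variance and allocation is balanced on them. The true standard error is then √(1 − R²) times the one an unadjusted analysis reports. With λ the standardised effect divided by √(2/n):

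- type I error, unadjusted: 2[1 − Φ(1.96/√(1 − R²))]
- power, unadjusted: Φ((λ − 1.96)/√(1 − R²))
- power, adjusted: Φ(λ/√(1 − R²) − 1.96)

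The effect is set to give 80% power at R² = 0: λ = 1.960 + 0.842 = 2.802, a standardised effect of 2.802 × √(2/72) = 0.467. This is a device for comparison, not a figure from the protocol.

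Example, R² = 0.20: 1/√0.80 = 1.118. Type I error is 2[1 − Φ(2.191)] = 2.8%. Power is Φ(0.842 × 1.118) = 82.7% unadjusted and Φ(2.802 × 1.118 − 1.96) = 87.9% adjusted.

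| Assumed R² | Reported / true SE | Type I error, unadjusted | Power, unadjusted | Power, adjusted | Points lost (from unrounded values) |
|---|---|---|---|---|---|
| 0 | 1.00 | 5.0% | 80.0% | 80.0% | 0 |
| 0.05 | 1.03 | 4.4% | 80.6% | 82.0% | 1.4 |
| 0.10 | 1.05 | 3.9% | 81.3% | 84.0% | 2.7 |
| 0.20 | 1.12 | 2.8% | 82.7% | 87.9% | 5.3 |
| 0.30 | 1.20 | 1.9% | 84.3% | 91.8% | 7.5 |

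A simulation of minimisation itself agrees (144 patients, preferred-arm probability 0.8, equally frequent factor levels, 3,000 runs per setting). At R² = 0.20, type I error is 3.2% unadjusted against 5.0% adjusted, and power is 82.4% against 87.6%. The mean reported standard error is 0.166, while the estimates actually vary with a standard deviation of about 0.15. At R² = 0.30, type I error is 2.2% against 5.2%, and power is 83.3% against 91.9%.

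**5. Binary outcome.** 50% versus 71%, 72 per arm, 1,500 runs per setting. An unadjusted chi-square test is compared with a Cochran-Mantel-Haenszel (CMH) test stratified by the two factors.

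| Assumed odds ratio per factor step | Type I error, unadjusted / stratified | Power, unadjusted / stratified |
|---|---|---|
| 1.5 | 5.5% / 5.7% | 73.3% / 73.5% |
| 2 | 4.2% / 4.7% | 73.4% / 75.3% |
| 3 | 2.6% / 4.9% | 77.5% / 82.3% |

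The Monte Carlo error of each power figure is about √(0.75 × 0.25/1500) = 1.1 points, so the row at 1.5 shows no visible loss.

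**The case against.** **Omission is inferred.** A reader might conclude that the two factors are definitely left out. The text does not say so: it contains no exclusion and no word such as only. The sentence before the rule already makes ANCOVA the analysis for measures, with covariates unnamed, and the confounder sentence can be read as adding to that model. A covariate list is also commonly left to the full protocol or analysis plan, which are not shown. This stands. What remains is that the one rule the article does state does not reach the factors that matter most.

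**Covariates chosen from observed imbalance.** A reader might infer that the model will be picked after inspecting the arms. The rule describes a class of factor and sets no test of imbalance. Unnamed covariates in a non-blind trial leave that possible, but the document does not prescribe it.

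**The comparator.** The tables set an analysis with neither factor against one with both. The planned ANCOVA has at least one covariate. If that is day-0 coverage, and it carries some of the same prognostic information as location or ABI, the further gain is smaller. This stands.

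**The size.** It rests wholly on an assumed prognostic strength and is nil if the factors do not predict outcome. This also stands. Choosing them for minimisation suggests that the investigators think them prognostic, but gives no figure.

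**False positives.** A reader might fear an inflated error rate. The opposite holds: the error is conservative, and a positive result would not be undermined.

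**Conclusion.** The point holds as a badly directed rule. It does not establish that the factors will be omitted. If they are prognostic and are omitted, type I error falls from 5% to about 2% across an assumed R² of 0 to 0.30, and about 0 to 8 points of power are lost in a continuous analysis. For a binary 50% versus 71% outcome the loss is about 0 to 5 points across assumed odds ratios of 1.5 to 3 per factor step. These figures assume near-balance on the two factors, 72 evaluable patients per arm, no centre effect and no other covariate. In a logistic model, adjustment need not shrink the standard error of the log odds ratio; the benefit there is in power and a correct type I error. The change should be made because it can only help and uses data already in hand, but the plan is not invalid without it.

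**What to change.** In Statistical methods {20a}, replace the rule about factors uncontrolled before allocation with a fixed statement. The primary ANCOVA includes ulcer location (three levels) and ABI stratum (above 0.7, or 0.7 and below), exactly as used in the minimisation, with day-0 coverage as a covariate, whatever the observed balance. For counts, put the same two factors in the logistic model or use them as CMH strata. Crossing them gives 3 × 2 = 6 strata. Crossing with the four centres as well would give 24, or 144/24 = 6 evaluable patients per stratum on average, so the logistic model may be more convenient.

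No new data are needed: location and ABI are recorded for allocation, and Table 1 schedules wound coverage on day 0. The cost is a dated amendment before the analysis. By the article's own dates, recruitment was expected to end in December 2022 and publication followed in October 2023. In a non-blind trial the record should therefore show that the model was fixed before the outcome data were analysed.

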### Oversight and monitoring

#### Quality control

Researcher authorization: All researchers are allowed to enter the trial and to conduct trial operations within the scope of authorization only after receiving training and authorization from the Principal Investigator.

Clinical monitoring: This clinical trial will be supervised by a clinical research auditor, who instructs the researchers to conduct the clinical trial in accordance with the trial protocol and GCP.

